### Role of diabetes

Diabetes mellitus is a widespread chronic disease with a global prevalence of 11.1% among adults aged 20 to 79 [12]. Diabetes mellitus is regarded as a risk factor for severe COVID-19, as indicated by increased rates of hospitalization, intensive care admission, and mortality [13]. However, it is not yet clear whether having diabetes per se is also a risk factor for developing Long/Post-COVID. A systematic review on this topic found that 44% of the studies identified diabetes as a risk factor for Long/Post-COVID, although the strength of this association varied considerably between studies [14]. This was partly due to the quality or design of the studies, e.g., a different definition of Long/Post-COVID, study population and study size, and the length of the observation period. In addition, no studies in Germany have yet compared the incidence of Long/Post-COVID in people with diabetes to people without diabetes.

People with diabetes exhibit chronic hyperglycemia, immune dysregulation, endothelial dysfunction, and a pro-inflammatory and prothrombotic state, which may exacerbate acute infection and promote persistent post-viral pathologies. In line with these mechanisms, studies suggest that diabetes mellitus may contribute to adverse long-term outcomes following SARS-CoV-2 infection including cardiovascular conditions [15, 16]. However, the association between diabetes and Long/Post-COVID, as well as its potential cardiovascular sequelae, remains incompletely understood.

Aims of this study are: 1) to estimate the incidence and time trends of Long/Post-COVID in people with diabetes compared to those without diabetes and to analyze potential risk factors for Long/Post-COVID; 2) to analyze mortality, any hospitalization, and hospitalization due to acute myocardial infarction, stroke, amputation, and DFS within 12, 24, and 36 months after Long/Post-COVID diagnosis in people with diabetes compared to those without, and to identify potential risk factors for these conditions.

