## Methods/design

### Study design and data sources

This study is planned as a non-interventional longitudinal observational study based on secondary data from the SHI in Germany. The data holder is the Health Data Lab which hosts SHI data and facilitates their analysis through secure remote processing.

The SHI data contains comprehensive information on inpatient and outpatient care with exact dates, diagnoses, prescriptions, and some sociodemographic factors (age, gender, place of residence (urban/rural)). The diabetes status of insured persons is defined according to an established algorithm based on antihyperglycemic prescriptions and outpatient and inpatient diagnoses [17]. A diagnosis of Long/Post-COVID is considered as first or incident event per se (no counting of reinfections), as this diagnosis has only been established since 2021. In light of the clinically heterogeneous presentation of Long/Post-COVID and the documented supposed inconsistencies in ICD-10 coding practices across healthcare settings, we define Long/Post-COVID on the basis of the following diagnostic coding: U08.9 (Personal history of COVID-19, unspecified; this code is used if a previous confirmed COVID-19 infection affects a person's health or leads to the use of healthcare services), U09.9! (Post-COVID-19 condition, unspecified;), U10.9 (Multisystem inflammatory syndrome associated with COVID-19, unspecified), or G93.3 (Myalgische Enzephalomyelitis/Chronisches Fatigue-Syndrom (ME/CFS). The Studies at Charité – University Medicine Berlin, which represent a major reference for research on Long/Post-COVID and ME/CFS, have shown that post-COVID syndrome can persist for more than 20 months after infection and encompass the full spectrum of post-infectious ME/CFS [18, 19]. The main features are moderate to severe fatigue and exercise intolerance, which meet the Canadian consensus criteria for ME/CFS.

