## Study participants

**Table Taba:** 

*Aim 1:*	*Participants*
Estimation of incidence and time trends of Long/Post-COVID in people with diabetes compared to those without diabetes, and analysis of potential risk factors for Long/Post COVID	All SHI-insured people in Germany (2021: 73.32 million; 2023: 74.31 million) stratified by diabetes status in the years 2021 to 2024
*Aim 2:*	
Analysis of mortality, any hospitalization, and hospitalization due to acute myocardial infarction, stroke, amputation, and DFS within 12, 24, and 36 months after Long/Post-COVID diagnosis in people with diabetes compared to those without diabetes, and identification of potential risk factors for these conditions	All SHI-insured people with and without an initial diagnosis of Long/Post-COVID, stratified according to diabetes status, will be monitored for a maximum of 36 months with regard to mortality and hospitalization due to relevant morbidity The cohort of Long/Post-COVID cases in 2021 and 2022 will be observed for up to 36 months; The cohort of Long/Post-COVID cases in 2023 will be observed for up to 12 months

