### Statistical analysis

*Aim 1* The incidence rate of Long/Post-COVID will be estimated separately in the population with and without diabetes and compared as relative risks. The incidence rates will be analyzed standardized by age and sex, using the entire German population as standard population. As SHI data will be used, the person time will be calculated by summing all quarters of the insurance time of insured persons under risk. The relevant insurance time ends on the earliest of the following: the date of first diagnosis of Long/Post-COVID (index date), the end of insurance time (e.g. death) or the end of the observation period (i.e. December 31, 2023).

In addition, Poisson regression models will be used to examine the time trend of the incidence rate of Long/Post-COVID. Since only 3 years will be available, we will only compare the incidence rates of 2022 and 2023 with those of the year 2021 as reference category. Moreover, the impact of potential risk factors such as age, sex, comorbidities (CHD, COPD, asthma, obesity, depression) and region (urban vs. rural, Eastern vs. Western Germany) will be analyzed with these models. We will consider each comorbidity as well as region separately in order to explore their role independently. We will estimate incidence rates stratified by diabetes and these variables. We further plan to perform regression models adjusted for each variable and diabetes as well as models stratified by diabetes. Thus, we intend to explore whether obesity is a further confounder or effect modifier in our analysis, even in the light of probable underreporting in administrative data. To take into account over-dispersion of the outcome variable, all analyses were conducted with the de-scale adjustment [22].

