*Aim 2* Age- and sex-standardized mortality and hospitalization rates will be estimated within 12, 24, and 36 months after a Long/Post-COVID diagnosis between 2021 and 2024. The data base will be a population-based cohort consisting of all insured persons with an inpatient or outpatient Long/Post-COVID diagnosis. All mortality and hospitalization rates will be calculated separately for insured people with and those without diabetes and will be compared using relative risks. In order to overcome potential confounding, Cox regression models will further be performed to investigate the impact of the aforementioned potential risk factors, as well as the year of Long/Post-COVID diagnosis. As we will conduct Cox models, we will only assess the time to first hospitalization with the date of hospital admission as index date. We will also consider death as competing risk in analyses with hospitalization as outcome.

Sensitivity analyses:Estimation of incidence rate of Long/Post-COVID in the population with and without diabetes and the corresponding relative risks as decribed in aim 1 using only insured persons with an outpatient or inpatient COVID-19 diagnosis as population at riskRepetition of analyses of aim 2 using only persons with an inpatient or outpatient Long/Post-COVID diagnosis and an additional previous COVID-19 diagnosis as population at riskExpansion of the outcome “Long/Post-COVID” to include comparable differential diagnoses (functional and somatoform disorders) in order to minimize the risk of bias resulting from potential underreporting of Long/Post-COVIDComparison of people with Long/Post-COVID and those with a differential diagnosis, stratified according to diabetes statusRepetition of main analyses of aim 1 and aim 2 with the modified outcome.

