## Abbreviations

SHI: Statutory health insurance
HDL: The health data lab
DFS: Diabetic foot syndrome
WHO: World health organization
ICD: International classification of diseases

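### The relative risk by diabetes status is also planned for diabetic foot syndrome, an outcome that presupposes diabetes, so that one Aim 2 comparison cannot be interpreted

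*Protocol article*

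**What the plan says.** The aims paragraph at the end of Role of diabetes lists DFS admission as an Aim 2 outcome in its own right and sets the contrast: "amputation, and DFS within 12, 24, and 36 months after Long/Post-COVID diagnosis in people with diabetes compared to those without". The Aim 2 row of the table under Study participants repeats the outcome list and the contrast: "within 12, 24, and 36 months after Long/Post-COVID diagnosis in people with diabetes compared to those without diabetes, and identification of potential risk factors".

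The Aim 2 text under Statistical analysis then gives one rule for every outcome: "All mortality and hospitalization rates will be calculated separately for insured people with and those without diabetes and will be compared using relative risks". It goes on to regression: "Cox regression models will further be performed to investigate the impact of the aforementioned potential risk factors, as well as the year of Long/Post-COVID diagnosis".

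Two other places matter. Study design and data sources explains the grouping: "The diabetes status of insured persons is defined according to an established algorithm based on antihyperglycemic prescriptions and outpatient and inpatient diagnoses". The Abbreviations section expands the outcome: "DFS: Diabetic foot syndrome". Nowhere is DFS restricted to people with diabetes or given its own rule. The limitations in the Discussion raise misclassification only for Long/Post-COVID coding.

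**The concern.** A relative risk compares how often an event occurs in two groups that could both have it. Here the grouping variable is part of the outcome's definition. A person truly without diabetes cannot have a diabetic foot, so the denominator of the planned ratio is zero by construction.

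If the tabulated denominator is not zero, the events in it have one of three sources: diabetes that the algorithm missed, a wrongly coded admission, or diabetes that began after status was assigned. None of these tells the reader how far diabetes raises the risk of DFS after a Long/Post-COVID diagnosis. At stake is one of six Aim 2 outcomes. Its ratio would be either missing or very large, and a very large ratio could be read as a substantive finding.

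**Working it through.** The article states no expected DFS rate, relative risk or sample size, so there is no figure of its own to reproduce. The check has three parts.

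**1. Perfect classification.** The number of DFS events without diabetes is 0, so the rate is 0 and the ratio is (rate with diabetes)/0, which is undefined. Age and sex standardization does not help, because a weighted mean of zero stratum rates is still zero.

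**2. Imperfect classification.** Let DFS occur at rate r in true diabetes and 0 otherwise. Let p be the diabetes prevalence and Se and Sp the sensitivity and specificity of the algorithm. Assume that Se is the same in people who develop DFS as in others with diabetes.

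- Observed rate in the group classed as having diabetes: r × PPV, with PPV = p·Se / [p·Se + (1−p)(1−Sp)].
- Observed rate in the group classed as not having it: r × (1−NPV), with 1−NPV = p(1−Se) / [p(1−Se) + (1−p)·Sp].
- Observed relative risk = PPV / (1−NPV). The rate r cancels.

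Inputs: p = 11.1% is the global adult figure in Role of diabetes, used only for illustration; 8% to 15% is an assumed range around it. All Se and Sp values are assumptions.

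Worked case with p = 0.111, Se = 0.90, Sp = 0.995:

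- PPV = 0.0999 / (0.0999 + 0.004445) = 0.957
- 1−NPV = 0.0111 / (0.0111 + 0.884555) = 0.01239
- Relative risk = 0.957 / 0.01239 ≈ 77

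Cross-check: with Se = 0.90, the share of DFS events that falls in the wrong group is f = 0.10, so (1−f)/f = 9. The ratio of group sizes is 0.895655 / 0.104345 ≈ 8.58, and 9 × 8.58 ≈ 77.

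| Assumed Se (p = 11.1%, Sp = 0.995) | Observed relative risk |
|---|---|
| 0.80 | 39 |
| 0.90 | 77 |
| 0.95 | 154 |
| 0.99 | 767 |
| 1.00 | undefined |

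Over p = 8% to 15%, Se = 0.80 to 0.99 and Sp = 0.98 to 1.00, the ratio runs from about 25 (p = 15%, Se = 0.80, Sp = 0.98) to about 1,151 (p = 8%, Se = 0.99, Sp = 1.00). It grows as the algorithm improves.

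**3. Cox model with a diabetes term.** A simulated cohort of 20,000 people, 11.1% of them with diabetes, had 60 DFS events, none of them without diabetes. The fit did not converge: log hazard ratio 25.2, standard error about 13,559. This is the usual result when one level of a covariate has no events. Within people with diabetes the term drops out, and age, sex, comorbidities, region and year of diagnosis remain estimable.

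**The case against.** The strongest reply is that this is an article. Outcome code lists and outcome-specific handling normally stand in the full protocol, which may already confine DFS to people with diabetes. The article gives no codes for DFS, so how firmly the reference group is empty depends on a definition that is not shown. That limits certainty about the observed count, but it does not remove the point: the published rule covers every hospitalization outcome, and the outcome's name requires diabetes.

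A reader might infer that the planned Aim 2 Cox models will break down. The documents do not support that. Those models use risk factors listed earlier, under Aim 1 (age, sex, five comorbidities, region), plus the year of diagnosis, and diabetes is not on the list. The sentence that does mention a diabetes term, "We further plan to perform regression models adjusted for each variable and diabetes as well as models stratified by diabetes", belongs to Aim 1 and also provides for stratified models, which would work for DFS. The Cox point is therefore conditional on a diabetes term being used.

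A reader might also infer that every DFS admission in the group without diabetes is an algorithm failure. With follow-up of up to 36 months, some could be true diabetes of later onset, and the article does not say whether status is fixed or updated.

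Finally, an empty or near-empty reference cell would be noticed at tabulation, and DFS is one outcome among six with none designated primary. Both are fair, and they bound the consequence.

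**Conclusion.** The point holds for the DFS between-group relative risk: as written, it is undefined or uninformative. This rests on DFS meaning what the Abbreviations section says and on the Aim 2 rule applying to every hospitalization outcome, as its wording states. It needs no numerical assumption. The range of 25 to 1,151 does rest on assumed accuracy and prevalence. It shows that the ratio is arbitrary and does not forecast this study's result.

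The defect is confined to that one comparison, and to any Cox model for DFS in which diabetes is a covariate. DFS rates and risk factors among people with diabetes remain valid. Death, admission for any cause, myocardial infarction, stroke and amputation can occur in both groups, so their comparisons stand, as does all of Aim 1.

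**What to change.** In the aims paragraph of Role of diabetes, the Aim 2 row of the Study participants table and the Aim 2 text of Statistical analysis, state that DFS is exempt from the comparison by diabetes status and from any model with diabetes as a covariate. State also that DFS rates and risk-factor models will be reported only among people with diabetes. Keep the other five outcomes, including amputation as the limb outcome, in the between-group comparison.

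The abstract's version of Aim 2 states no contrast by diabetes status, so it needs no rewording on this account. A comparison of people with and without Long/Post-COVID within diabetes is not required. The Aim 2 analysis text builds its cohort from people with a Long/Post-COVID diagnosis, so such a contrast would need a comparator cohort that this text does not include.

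The cost is a few words in three places and one fewer between-group outcome. No additional data are needed.

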## Discussion

Our project will contribute to gaining new insights into open questions regarding the association between diabetes and Long/Post-COVID. The results of the study will provide reliable epidemiological data on the incidence, relative risk, and time trends for Long/Post-COVID in people with diabetes which might influence health research and health policy decisions. Results will be reported in accordance with the STROSA guidelines [23].

Several expected limitations should be considered. Misclassification cannot be excluded, as the validity of coding for Long/Post-COVID conditions may vary due to differences in awareness and documentation practices across healthcare settings. Furthermore, the lack of information about the severity of symptoms could influence the risk assessment. Residual confounding cannot be excluded, as factors such as vaccination status could not be taken into account. Moreover, our analyses will not be further stratified by diabetes type since this would cause statistical power problems due to the expected small sample size.

## Data Availability

No datasets were generated or analysed during the current study.

## Abbreviations

SHI: Statutory health insurance
HDL: The health data lab
DFS: Diabetic foot syndrome
WHO: World health organization
ICD: International classification of diseases
